#### Analyses of secondary outcomes

For the three time-to-event outcomes of NAFLD-associated admissions and re-presentations, and first fibrosis assessment, we will use Kaplan–Meier plots and Weibull survival models as per the primary outcome.

For health-related quality of life we will model the participants’ 12-month result whilst adjusting for their baseline, which is the equivalent to examining the within-participant change in quality of life and helps adjust for regression to the mean [19, 20]. We will use a linear regression model and check the model residuals.

Statin use will be compared between groups by examining the number of participants given a new statin script during the follow-up period. The denominator will be the number of patients not on statins at the time of their referral letter to the hepatology clinic. We will compare the numbers using a 2-by-2 table and Chi-squared test. Deaths and HCC detection will be compared between groups using a 2-by-2 table. As these two outcomes are likely to be rare, we anticipate needing to use Fisher’s exact test to look for statistical differences between the two groups.

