## Methods

### Study design

#### Parallel randomised trial

We will conduct a 1:1 parallel randomised trial to compare two alternative models of care for NAFLD. Participants will be randomised to usual care or the LOCal Assessment and Triage Evaluation (LOCATE) model of care and followed for 1 year to monitor their outcomes.

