#### Data management

#### Data sources

Data for outcomes involving contact with tertiary care will be collected from Queensland Health administrative databases.

For the economic evaluation, a state-based model will be developed. Costing data will be prospectively collected from multiple sources to measure costs associated with; hospital utilisation, pharmaceutical and primary care use, and patient travel costs, lost productivity and other out-of-pocket expenses. To estimate health utility, quality of life data will be collected using the EuroQol EQ-5D-3 L tool and assigned to each health state in the model. Data will be collected from participants at two time points, as previously described.

For the implementation objectives, we will audit data collected throughout the study, and conduct semi-structured interviews with key stakeholders and consumers. These interviews will occur within 8 weeks of the trial’s conclusion.

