### Statistical analysis

#### Sample size and statistical power

We have a minimum total sample size of 156 participants for our primary outcome of time to diagnosis, but we will aim for a sample size of 234. Two hundred and 34 participants will give us a 95% power to detect a 50% reduction in the primary outcome of time to diagnosis of high-risk disease. Our lower sample size of 156 gives us an 83% power. We used a two-sided 5% significance level. We assumed an average diagnosis time of 180 days in the usual care group, and a halving of this time in the intervention group. We assumed that 5% of participants would be censored due to death or loss to follow-up. The sample size was estimated by simulating survival data using the “sim.survdata” function from the “coxed” package in *R* using 1000 simulations [16]. We assumed a log-normal hazard function with a standard deviation of 10 days. The statistical code to run the sample size is available here: https://github.com/[name]/LOCATE. We assume that half of all patients approached will agree to participate, hence, we aim to approach 468 people.

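### Hospital admissions and emergency presentations can recur and are listed as things to reduce, but the stated analysis is a single-event survival analysis, and the outcome is worded differently in the two places

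*Protocol article*

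**What the plan says.** Secondary clinical outcomes lists, among other aims, a reduction in hospital admissions and a reduction in emergency department presentations. It defines neither as a count, a rate or a first event, and limits neither to liver-related causes. Where that list means a time, it says so, as for the first successful fibrosis assessment and for further liver testing.

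Analyses of secondary outcomes then states: "For the three time-to-event outcomes of NAFLD-associated admissions and re-presentations, and first fibrosis assessment, we will use Kaplan–Meier plots and Weibull survival models", and adds "as per the primary outcome". The primary outcome is a single event per person, a diagnosis of high-risk disease. No count, rate, frailty or other recurrent-event model is named for admissions or presentations.

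On the data, the article says: "Data for outcomes involving contact with tertiary care will be collected from Queensland Health administrative databases". Participants are "followed for 1 year to monitor their outcomes".

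**The concern.** An admission or an emergency visit can occur several times in a year. A Kaplan–Meier curve and a Weibull model fitted as for a diagnosis use one event per participant, so a person admitted five times counts the same as a person admitted once. That answers whether the event was avoided or delayed. It does not answer whether there were fewer events, which is the natural reading of the listed aim and of the article's motivation (hospital burden and avoidable admissions).

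Three things are at stake. The reported clinical estimate may not address the listed aim. It may be less precise than the data allow. And it could point differently from the economic evaluation, which draws on hospital utilisation costs.

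A separate textual problem sits on top of this. The aims speak of admissions and presentations without restriction, while the analysis section speaks of NAFLD-associated admissions and of re-presentations. Neither term is defined, so it is unclear which events are to be analysed at all.

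**Working it through.** **Figures in the plan.** No event rate, effect size or power is given for admissions or presentations, so there is no figure on this point to reproduce. The stated powers ("Two hundred and 34 participants will give us a 95% power to detect a 50% reduction in the primary outcome"; "Our lower sample size of 156 gives us an 83% power") concern time to diagnosis only and do not bear on it.

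**Inputs from the article.** Target of 234 participants, 1:1, so 117 per arm; one year of follow-up; two-sided 5% level.

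**Assumptions, none in the article.** True rate ratio 0.70; usual-care rate λ of 0.2 to 2.0 events per person-year; gamma variation in underlying rate between participants with variance k from 0 to 4; no deaths or withdrawals.

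**Step 1: how many events a first-event analysis uses.** The chance of at least one event in the year is 1 − exp(−λ) if k = 0, and 1 − (1 + kλ)^(−1/k) otherwise. Total expected events are 117 × λ × 1.7.
- λ = 0.2, k = 0: 117 × (0.181 + 0.131) = 36.5 first events of 39.8, so 8% unused.
- λ = 1, k = 0: 117 × (0.632 + 0.503) = 132.9 of 198.9, so 33% unused.
- λ = 2, k = 4: 117 × (0.423 + 0.376) = 93.5 of 397.8, so about 77% unused.

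**Step 2: power.** Simulation with 600 trials per cell (simulation error about 2 points), comparing a Weibull model of the first event with a negative binomial model of all events:

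| Usual-care rate per year | k | Weibull HR (median) | Power, first event | Power, count |
|---|---|---|---|---|
| 0.2 | 0 | 0.68 | 21% | 20% |
| 0.2 | 2 | 0.71 | 14% | 18% |
| 0.2 | 4 | 0.75 | 12% | 15% |
| 0.5 | 0 | 0.71 | 33% | 37% |
| 0.5 | 2 | 0.76 | 21% | 29% |
| 1.0 | 0 | 0.70 | 52% | 70% |
| 1.0 | 2 | 0.78 | 23% | 36% |
| 2.0 | 0 | 0.70 | 67% | 92% |
| 2.0 | 2 | 0.81 | 24% | 41% |
| 2.0 | 4 | 0.86 | 15% | 23% |

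Hand check at λ = 1, k = 0:
- First event: |ln 0.70| × √(132.9/4) = 0.357 × 5.76 = 2.06, and Φ(2.06 − 1.96) = 54%.
- Count: standard error √[(1/1 + 1/0.7)/117] = 0.144, ratio 0.357/0.144 = 2.48, and Φ(2.48 − 1.96) = 70%.

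Both agree with the simulation within its error. Across all cells at 1 to 2 events per year the gap is 8 to 25 points. At 0.2 per year it is about 0 to 4.

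A second simulation used a rate ratio of 0.50 and k of 0.5, 1 and 2. At 1.0 event per year, power was 85% v 96%, 78% v 91% and 56% v 80% (first event v count). At 0.1 to 0.2 per year the gain was 0 to 6 points. With no true effect, both methods rejected in 4 to 7.5% of trials.

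**Step 3: the estimate itself.** With gamma variation, the cumulative hazard of a first event by one year is ln(1 + kλ)/k. For k = 1, λ = 1 and a rate ratio of 0.50, the ratio of cumulative hazards is ln(1.5)/ln(2) = 0.405/0.693 = 0.585. With k = 0 it equals the rate ratio exactly. The move towards 1 therefore appears only when participants differ in underlying risk.

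**The case against.** The strongest reply is that the loss may be negligible here. The analysis section restricts admissions to NAFLD-associated ones. The Background puts 60 to 90% of patients with NAFLD as free of advanced fibrosis, and the exclusion criteria remove those needing priority review. Low rates are therefore plausible for admissions, and at about 0.2 per year almost nothing is lost. This stands. It does not settle the matter for emergency presentations, or for admissions if the unrestricted wording in the aims is the intended one. The article calls only deaths and HCC detection likely to be rare.

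Time to first event is also a valid target. Over a fixed year the Kaplan–Meier curve shows the proportion ever admitted, and fewer people admitted is one kind of reduction. This stands too: the hazard ratio and the rate ratio are different quantities, and neither is a biased version of the other.

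A reader might infer that the plan throws away every repeat event. The article does not say so. It is inferred from the method; the word first is attached only to the fibrosis assessment, and re-presentations could itself mean repeat events. Nor are hospital data wasted, since hospital utilisation feeds the economic evaluation.

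Finally, the simulations generate data from the model they favour, with a constant effect over repeats and no deaths, and they did not test the influence of a few very frequent attenders. The gains are best read as indicative.

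**Conclusion.** The point holds as a mismatch between aim and analysis. The aims speak of reducing events that can recur, the named method estimates time to one event, and the two sections disagree on which events are meant. This concerns a method the article states, not a detail left to another document.

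The consequence is conditional. At an assumed 1 or more events per person-year, a first-event analysis can give up roughly 8 to 25 points of power (rate ratio 0.70, 234 participants). If underlying risk varies, its hazard ratio lies nearer to 1 than the rate ratio. At about 0.2 per year or below, little is lost.

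A reader might go further and conclude that the plan necessarily loses power and shrinks the effect. The documents do not support that, because they give no event rate, effect or dispersion for these outcomes. No stated figure is wrong, since power is claimed only for the primary outcome. This is a cheap improvement to secondary analyses, not an error that threatens the trial.

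**What to change.** Use the same definition of each outcome under Secondary clinical outcomes and Analyses of secondary outcomes. Say whether admissions are all-cause or NAFLD-associated, and whether the emergency outcome is presentations or re-presentations.

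Then add to the analysis section, for admissions and for emergency presentations separately: the number of episodes per participant over 12 months, analysed with a negative binomial model with log person-time at risk as offset (so that death and withdrawal shorten exposure) and robust standard errors, reported as a rate ratio with 95% CI. Keep the Kaplan–Meier plot and Weibull model of the first event alongside, labelled as first event. The analysis of time to first fibrosis assessment needs no change.

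The cost is some wording and one extra model per outcome, on data the plan already draws from administrative databases. If the NAFLD-associated definition is kept, the plan should also state how episodes are attributed to NAFLD. The count model can be sensitive to a few frequent attenders, which robust standard errors limit but do not remove, and it gains little if events prove rare.

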#### Twelve-month chart audit

Study nurses will audit the patients’ individual medical record at 12 months post-recruitment and extract much of the data needed for the primary and secondary outcomes.

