#### Blinding

It is challenging to hide the randomised group because this is an open-label study where both the participants and researchers will be aware of what group participants are in. Baseline data will be collected blind to randomised group, as it will be done prior to randomisation.

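### The secondary analyses of admissions, emergency presentations and HCC use different event definitions from the outcome list, and the added terms are undefined

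*Protocol article*

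**What the plan says.** The list under Aims, Secondary clinical outcomes, names fewer hospital admissions and fewer emergency department presentations, neither tied to a cause. It also names HCC, but only HCC found outside specific surveillance.

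Analyses of secondary outcomes opens its time-to-event paragraph with "For the three time-to-event outcomes of NAFLD-associated admissions and re-presentations, and first fibrosis assessment", to be handled with Kaplan–Meier plots and Weibull models. For HCC it says "Deaths and HCC detection will be compared between groups using a 2-by-2 table", and it expects to need Fisher's exact test because events will be rare. No other analysis of these three outcomes is given.

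Three further places bear on how the events would be classified:
- Blinding: "this is an open-label study where both the participants and researchers will be aware of what group participants are in". Only baseline data are described as collected blind.
- Twelve-month chart audit: study nurses will "extract much of the data needed for the primary and secondary outcomes".
- Data sources: "Data for outcomes involving contact with tertiary care will be collected from Queensland Health administrative databases".

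**The concern.** An outcome list and its analysis section should describe the same events. Here they differ for three secondary outcomes, and not in one direction: admissions gain a cause restriction, while HCC loses its restriction to cases outside surveillance. An analyst could follow either section and claim to be following the protocol.

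Two consequences matter. First, a cause label has to be assigned by someone or something. LOCATE puts a fibrosis result before the hepatologist and GP while usual-care patients are still waiting, so the information behind a NAFLD label can reach the record earlier in one arm. Second, the Fibroscan service is described as identifying people who need liver cancer surveillance. If it does so, HCC found outside surveillance may fall while total HCC found does not fall, or rises. A count of all HCC would then not show the benefit that the outcome list describes.

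**Working it through.** **Step 1: set the two sections side by side.**

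| Outcome list (Secondary clinical outcomes) | Analysis (Analyses of secondary outcomes) | Change |
|---|---|---|
| Hospital admissions, no cause stated | NAFLD-associated admissions | Narrowed; term undefined |
| Emergency department presentations, no cause stated | Re-presentations | Renamed; term undefined; unclear whether the NAFLD restriction carries over |
| HCC outside specific surveillance | HCC detection | Widened |

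The analysis section counts three time-to-event outcomes. They line up with three listed items: admissions, emergency presentations and first successful fibrosis assessment. It is therefore the analysis of the listed outcomes and not of an additional set.

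**Step 2: is the admissions difference more than wording?** The article gives no admission rates, so there is no stated figure to reproduce and what follows is illustration on assumed values. Suppose LOCATE halves the hazard of NAFLD-associated admissions and leaves other admissions unchanged. If a share f of admissions is NAFLD-associated, then approximately HR(any admission) = 1 − 0.5f. Events for 80% power at two-sided 5% with 1:1 allocation (Schoenfeld) are 4(1.960 + 0.842)² / (ln HR)².

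| Assumed f | HR, any admission | Events needed |
|---|---|---|
| 100% | 0.50 | 66 |
| 50% | 0.75 | 380 |
| 25% | 0.875 | 1,761 |
| 10% | 0.95 | 11,933 |

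The same effect of the service gives very different answers under the two definitions. They are different estimands.

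**Step 3: precision against dilution.** Take the target sample of 234 and assume that 20% have any admission (0.20 × 234 ≈ 47 events) and 3% a NAFLD-associated one (0.03 × 234 ≈ 7 events). With SE(ln HR) = 2/√events:
- 47 events: SE = 0.292, and the 95% CI is the estimate times or divided by exp(1.96 × 0.292) = 1.77.
- 7 events: SE = 0.756, and the factor is exp(1.96 × 0.756) = 4.40.

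The restricted outcome is far less precise, but precision is not the whole comparison. Under the Step 2 effect, f = 7/47 = 0.149. The any-admission HR is 1 − 0.5 × 0.149 = 0.93, so |z| = |ln 0.926|/0.292 ≈ 0.27. For the restricted outcome |z| = |ln 0.50|/0.756 ≈ 0.92. In this scenario the restricted outcome carries more signal, and neither outcome comes near significance.

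**Step 4: what differential labelling could do.** If true admission risk is equal in both arms, the apparent risk ratio for labelled admissions equals the ratio of the labelling proportions. Equal labelling gives 1. With an assumed 20% risk in each arm, and 20% of LOCATE but 10% of usual-care admissions labelled, the result is 0.20 × 0.20 = 4% against 0.20 × 0.10 = 2%, a spurious ratio of 2. Nothing in the article indicates where in that range the trial would fall.

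**Step 5: HCC.** No arithmetic applies. Total HCC is the sum of cases inside and outside surveillance. A service that moves people into surveillance can shift cases from the second group to the first, so the total need not move with the listed outcome.

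**The case against.** The strongest reply is that the outcome list is terse and the analysis section is its working version: *HCC detection* is shorthand, and a disease-specific admission outcome fits the aim, under Secondary economic outcome, of reducing costly hospital complications. The article also condenses a fuller document that may define the terms. This explains how the difference may have arisen but does not remove it. Both sections are current text, they name different events, and nothing says which governs.

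Several stronger readings are tempting and should not be adopted:
- *That admissions were listed as all-cause.* The term is not used. They are listed without a cause, and all-cause is only the plain reading.
- *That the analysis relies on unblinded attribution.* No method of attribution is stated. Tertiary-care contacts come from administrative databases, so routine coding is possible, and the chart audit is not tied to particular outcomes. Coding would lessen the risk without fully removing it, since codes follow what has been documented.
- *That re-presentations are analysed only in a subset formed after randomisation.* In context the word most plausibly labels the emergency presentation item.
- *That the HCC result will reverse.* It could. But HCC is expected to be rare, follow-up is one year, and patients needing priority review, such as those with imaging suggesting cirrhosis or a focal lesion, are excluded.
- *That unrestricted admissions are simply the better outcome.* Step 3 shows a plausible case where they are not.

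**Conclusion.** The inconsistency stands on the text alone and needs no assumed rate: for admissions, emergency presentations and HCC, the event to be analysed is not the event listed. *NAFLD-associated* and *re-presentation* are undefined, and no rule-based or blinded attribution is stated in an open-label trial. Differential attribution is therefore a risk and not a demonstrated bias.

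The size is unknown. The hazard ratios of 0.50 to 0.95, the CI factors of 1.77 and 4.40, and the spurious ratio of up to 2 all rest on assumed shares, rates or labelling proportions. They show only that the choice of definition matters. The primary outcome and the sample size are unaffected. This should be corrected because it determines what three secondary analyses can conclude.

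**What to change.** Reconcile Secondary clinical outcomes with Analyses of secondary outcomes. In the analysis section:
1. **HCC:** count HCC detected outside surveillance as the outcome, and show total HCC beside it.
2. **Emergency care:** replace *re-presentations* with emergency department presentations.
3. **Admissions:** analyse hospital admissions as listed, from the Queensland Health databases in both arms. Report NAFLD-associated admissions alongside, defined by a diagnosis-code list fixed before data extraction and applied without regard to arm.

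If the disease-specific version of admissions is the intended outcome, amend the outcome list to say so, keep the fixed code list, and report any admission beside it.

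The cost is a change of wording and the drawing up of a code list; the administrative data are already being obtained. For HCC, each case must also be classified as inside or outside surveillance, which the listed outcome already requires. The drawback is that unrestricted admissions include events the service cannot affect and so dilute a disease-specific effect, which is why both versions should be reported.

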### Study population

#### Patient inclusion criteria

Patients will be included if they:
Have had NAFLD diagnosed or suspected by their GP.Are aged 18 years or over.Understand the consent procedures and give their full consent.Consent to access of their data from Queensland Health and Medicare Benefits Schedule (MBS) and Pharmaceutical Benefits Scheme (PBS).

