### Description of all processes

#### Data collection

#### Referral letter

Date of referral, age, BMI, presence of type 2 diabetes and relevant blood tests such as AST, ALT, albumin, platelet count, viral serology, ferritin and transferrin saturation will be extracted from the referral letter.

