#### Recruitment and consent

#### Recruitment

Potential participants will be identified based on the referral letter sent from their GP to the hepatology clinic. Potentially eligible participants will be sent a letter containing an invitation to participate and the contact details of a study nurse.

NEGATIVE OR NO RESPONSE: If no response to the initial letter is received after 2 weeks, a study nurse will contact the patient by phone. If the potential participant does not answer the phone, an SMS will be sent from a study phone to their mobile, informing them that it was a study nurse who called, and providing a brief explanation of the study and contact information. If at any stage of this process they state they are not interested, they will not be contacted again.

POSITIVE RESPONSE: Those interested in participating will be able to call a study nurse to discuss the trial. Interested participants will then be mailed the Participant Information and Consent Form, MBS/PBS consent forms, withdrawal form, study questionnaires, a $20 voucher and a reply-paid return envelope.

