#### Consent

Potential participants who agree to be contacted after the recruitment process will be sent the study forms in the mail and asked to read, sign and return the forms using the reply-paid envelope. The study nurses will make one follow-up call, and SMS if not answered, to potential participants who have not returned the consent and enrolment questionnaires after 2 weeks. We will record the number of participants declining to consent and will also record the number of potential participants who could not be contacted.

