#### Randomisation

A 1:1 randomisation list will be created by the study statistician in the *R* software. The list will be stratified by health service (Sunshine Coast and Metro South) and will be in randomised blocks of size 6 and 8. This creates balanced groups over time and means that group sizes will be approximately equal if recruitment ends early. The list will be uploaded into the REDCap software [15]. Patients will be randomised once they have returned the signed consent form and questionnaires.

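### Statin-free status is fixed at the referral letter rather than at randomisation, so statin starts between the two dates dilute the new-statin comparison

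*Protocol article*

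**What the plan says.** The section on analyses of secondary outcomes defines the statin comparison in three sentences. The numerator: "Statin use will be compared between groups by examining the number of participants given a new statin script during the follow-up period". The denominator: "The denominator will be the number of patients not on statins at the time of their referral letter to the hepatology clinic". The test: "We will compare the numbers using a 2-by-2 table and Chi-squared test".

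The Randomisation section places allocation later than the letter: "Patients will be randomised once they have returned the signed consent form and questionnaires". Before that point, the hepatologist screens the referral letter and an invitation is mailed. The Recruitment section then adds "If no response to the initial letter is received after 2 weeks, a study nurse will contact the patient by phone". After that the forms are mailed, and the Consent section provides one more call to "potential participants who have not returned the consent and enrolment questionnaires after 2 weeks".

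The Study design section attaches the one year of follow-up to the randomised groups, and the chart audit is timed at 12 months after recruitment. The statin paragraph does not define a new script and does not say when follow-up starts for this outcome.

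**The concern.** The at-risk set and the counting of events use different clocks. Membership of the denominator is decided at referral, while the events of interest are those that the model of care could influence, which means events after allocation. A statin started in between belongs to neither arm's care, yet the patient who started it remains in the 2-by-2 table.

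The referral visit is a time when a GP is already thinking about the patient's metabolic risk, so some starts in this interval are plausible, although the article gives no figure. At stake is the sharpness of one listed secondary outcome, increased statin use. The validity of the randomised comparison is not in question, because both possible anchor dates precede allocation.

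**Working it through.** **No figure to reproduce.** The article states no statin prevalence, start rate, effect size or power for this outcome. Its power figures (95% at 234 participants, 83% at 156) concern time to diagnosis.

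**Step 1: order of dates.** Referral letter, screening of the letter, invitation (call if no reply after 2 weeks), mailed forms (call if not returned after 2 weeks), return of forms, randomisation, one year of follow-up. The gap exists for every participant. The total interval is not stated.

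**Step 2: what happens to a patient who starts a statin in the gap.** The patient was not on statins at referral, so is in the denominator under every reading:

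- Follow-up read as running from referral: the start is an event that allocation cannot have caused.
- Follow-up from randomisation, a later script read as new: the same false event.
- Follow-up from randomisation, a later script not read as new: the patient is in the denominator but cannot become a case.

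No reading removes the problem.

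**Step 3: direction.** Let m be the share of the denominator that started in the gap, the same in both arms in expectation. Let p1 and p2 be the true start rates after randomisation in usual care and LOCATE, and let c be 1 if gap starters are counted as new and 0 if not. The expected observed rate in arm i is

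q_i = (1 − m) × p_i + m × c

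so q2 − q1 = (1 − m) × (p2 − p1) for either value of c. The absolute difference always shrinks by the factor (1 − m). The ratio q2/q1 is unchanged if c = 0 and moves toward 1 if c = 1.

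**Step 4: illustration with assumed inputs.** Assumed: p1 = 10%, p2 = 25%, two-sided 5%, and 117 per arm (234 ÷ 2, an upper bound, because participants already on statins are excluded). Power uses the usual normal approximation with pooled variance under the null:

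power = Φ{ [ (q2 − q1) − 1.96 × √(2q̄(1 − q̄)/n) ] ÷ √((q1(1 − q1) + q2(1 − q2))/n) }, with q̄ = (q1 + q2)/2.

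| m | difference (points) | c = 0: rates, ratio, power | c = 1: rates, ratio, power |
|---|---|---|---|
| 0 | 15.0 | 10.0% v 25.0%, 2.50, 86% | same |
| 1.6% | 14.8 | 9.8% v 24.6%, 2.50, 85% | 11.4% v 26.2%, 2.29, 83% |
| 5% | 14.25 | 9.5% v 23.75%, 2.50, 84% | 14.5% v 28.75%, 1.98, 76% |
| 10% | 13.5 | 9.0% v 22.5%, 2.50, 81% | 19.0% v 32.5%, 1.71, 66% |

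The 1.6% row assumes an 8-week gap and a constant start rate equal to the assumed 10% a year: 1 − 0.90^(8/52) = 0.016. The 5% and 10% rows would need a longer gap or a cluster of starts around the referral visit. With a smaller denominator of 60 per arm (assumed), power starts at 58%; at m = 5% it is 56% (c = 0) or 47% (c = 1).

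**The case against.** The case for leaving the text alone has four parts.

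- **Referral is the trial's own clock.** The primary outcome is timed from GP referral, so anchoring statin status there is consistent. This explains the choice but does not rescue it. A time origin for a duration is a different thing from the at-risk date for an event meant to be influenced by allocation.
- **A repeat script is not naturally new.** This stands in part. If gap starters are never counted as new, the ratio is preserved and only the absolute difference and the power fall. They still sit in the denominator as people who cannot become cases.
- **The gap may be short.** This stands. The only intervals stated are two 2-week reminder points, and at a constant start rate an 8-week gap gives a share of about 1.6%.
- **The effect is balanced.** This also stands. Status before randomisation is the same in both arms in expectation, so the consequence is dilution and not a shift in favour of one arm.

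A reader might infer more: neither the items extracted from the referral letter nor the recruitment questionnaire lists medicines, so patients already on statins at referral would be misclassified as non-users. The document does not support that. The rule names a date, not a source. Consent to PBS data is an entry criterion, nurses audit the medical record at 12 months for secondary outcome data, and pharmaceutical use is collected for costing. Any of these could supply status at referral, and an article may leave the choice of source to the full protocol or analysis plan.

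**Conclusion.** The concern holds in a narrow form. The stated rule fixes the at-risk group at a date before randomisation, so statin starts in the gap are kept in the denominator with no valid role there. The rule is stated and not merely left open, so an analysis plan that followed it would inherit the mismatch.

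The consequence is minor: a modest dilution of one secondary outcome, equal across arms in expectation, with no threat to the primary outcome. The documents do not allow its size to be computed. Under the assumed rates above, the loss in absolute difference is between 0.2 and 1.5 percentage points out of 15 for gap shares of 1.6% to 10%. The loss of power is larger only if every gap starter is also counted as a new user, which the wording does not establish. A large fall in the ratio should therefore not be claimed.

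**What to change.** Reword the statin outcome as follows:

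- Denominator: participants not on statins at randomisation.
- Outcome: first statin script or dispensing after randomisation and within 12 months.
- Source of status and outcome: PBS data, the chart audit or both, named in advance, with a pre-stated look-back for deciding who is statin-free.

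The length of the look-back and the choice between scripts and dispensings are for the sponsor; the documents do not force either. The 2-by-2 comparison can stay as it is.

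The cost is a change of wording and, if PBS is used, an extract that reaches back before randomisation. Consent to PBS data is already required, but the article does not state the period covered, so this should be checked. The denominator becomes slightly smaller, and with PBS as the source, scripts that are written but not dispensed are missed.
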